## Abstract

**Background:** Early childhood obesity is an urgent public health challenge, with long-term health risks. The 12-month fruehstArt intervention aims to improve healthcare for 3 to 6-year-olds with overweight and obesity in Germany through a family-centred approach, including home-based counselling with coaches, paediatric consultations, and a supportive web application for both German- and Turkish-speaking families. This process evaluation will examine the barriers and enabling factors critical for successful implementation, identify necessary adaptations to the intervention, and assess its quality and acceptability among families, coaches, and paediatricians. **Methods:** This formative evaluation will use a mixed-methods approach including qualitative and quantitative data. Semi-structured interviews will be conducted with parents, coaches, and paediatricians at two different time points. Interviews will be analysed using qualitative content analysis. An Implementation Quality Index assessing the four dimensions of dosage, adherence, quality of delivery, and participant responsiveness will be developed, based on data collected from coaches carrying out the home-based counselling and participating parents of the intervention group. Linear mixed models for repeated measures will be used to analyse the relationship between data of the Implementation Quality Index and the primary and secondary outcomes of the effectiveness evaluation. **Conclusions:** The formative evaluation of the fruehstArt intervention is expected to identify important determinants of the implementation and provide valuable insights for future strategies to improve implementation. By identifying barriers and facilitators to participation, this study aims to pave the way for an effective dissemination of the intervention and ultimately contribute to improved health outcomes for children.

## 1. Introduction

Overweight and obesity are major global health challenges, affecting the physical, mental, and social well-being of millions of people [1,2]. In 2022, the World Health Organization (WHO) highlighted that worldwide more than 37 million children under the age of five were overweight [3]. Childhood obesity is associated with an increased risk of serious health problems in adult age such as cardiovascular diseases, diabetes mellitus, and mental disorders, which impact educational success and increase the risk of persistent obesity into adulthood [4,5,6,7,8,9]. Selective and indicated prevention strategies in early childhood are therefore crucial to mitigate its adverse short- and long-term effects and to promote healthier lives in adulthood [10].

The German Health Interview and Examination Survey for Children and Adolescents (KIGGS) found that approximately 14% of girls and 8% of boys in Germany aged 3 to 6 years are overweight or obese, with the prevalence varying by age, gender, and socioeconomic status (SES) [11]. Furthermore, the COVID-19 pandemic has exacerbated this problem, contributing to an increase in overweight and obesity in children and adolescents due to increased sedentary behaviour (e.g., screen time), reduced physical activity, and altered dietary habits [12].

The causes of childhood overweight and obesity are linked to genetic, psychological, social and environmental factors, as well as family and lifestyle habits such as eating patterns, physical activity and media consumption [13,14,15]. This underlines the importance of early intervention within the family setting, where habits are formed and can be most effectively influenced. Parents, as the primary architects of the family environment, play a key role in establishing these habits, highlighting the necessity of their involvement in interventions to prevent overweight and obesity [16,17,18]. By focusing on the family as a key setting for intervention, there is a great opportunity to address childhood overweight and obesity in a holistic and impactful way [19]. Paediatricians and other healthcare providers also play a crucial role in offering expert guidance to families and ensuring tailored, comprehensive approaches to prevention [20].

In Germany, the current care situation for children with overweight and obesity is characterised by insufficient and regionalised services with limited reach [21]. For the age group 3 to 6 years, there is no structured care in place, which represents a significant gap in research and intervention efforts [22]. Therefore, a family-centred, cross-sectoral care and prevention programme called fruehstArt, has been developed, specifically aiming at an early reduction of overweight and prevention of obesity in children. The fruehstArt programme is therefore conceptualised as a preventive approach that includes both overweight and obese children. While it does not represent primary prevention in the strict sense, its main objective is to prevent further weight gain among overweight children and to avoid the persistence of obesity into adolescence and adulthood among those who are already obese. Thus, fruehstArt combines elements of secondary and tertiary prevention, aiming to reduce long-term health risks through early, family-based lifestyle and behavioural interventions.

The aim of this part of this study is to conduct a formative evaluation of fruehstArt at the process level to analyse context-specific barriers and enabling factors that are critical for the implementation of the intervention, and to identify adaptions to the intervention’s structure as well as possible modifications in the implementation concept. It seeks to enhance understanding of the intervention’s implementation quality and factors influencing its acceptability among families, coaches, and paediatricians.

## 2. Methods

### 2.1. The FruehstArt Intervention

FruehstArt offers an innovative intervention for families with children aged 3 to 6 years who are overweight (Body Mass Index (BMI) > P (Percentile) 90) or obese (BMI > P97) or a sudden weight gain with a BMI-SDS (BMI Standard Deviation Score) increase of 0.2/year is detected, which is classified as a cause for concern by the paediatrician [23].

Given that empirical studies have found a higher prevalence of overweight and obesity among children from families with a migration background [24], fruehstArt addresses not only German-speaking but also Turkish-speaking families, which is the group with the highest percentage of migrants in Germany [25]. To support access to this population group, fruehstArt engages Cologne neighbourhood mothers—trained women with relevant cultural backgrounds—to facilitate community access and support coaches in their endeavour.

To achieve fruehstArt’s primary aim of reducing childhood overweight and obesity, it promotes physical activity, a balanced diet, healthy sleep patterns and an age-appropriate use of media. To achieve this aim, families participate in home-based coaching sessions conducted by trained coaches, who offer tailored counselling within the family context to meet the distinct needs of each family. These coaches cooperate with each child’s paediatrician to develop a customised counselling plan. Moreover, aligned with the socio-ecological approach of overweight and obesity, the coaches help families to identify and make use of regional health services [26,27]. These include e.g., sports clubs close to their homes, addressing environmental and community-level factors that support healthy behaviours. This introduces an innovative model of cross-sectoral support, merging behavioural and community-based support measures, thereby representing a comprehensive and tailored approach to healthcare for families.

Children are assigned to one of six coaching strands depending on the child’s BMI percentile and individual support needs [28]. Based on the individual needs of the family the number of coaching sessions varies, ranging from 10 to 20 home visits within the 12-month intervention period. Additionally, those with a BMI above the 97th percentile are offered a six-week inpatient rehabilitation service or a newly developed outpatient rehabilitation service, available twice a week for six months near their home. However, the rehabilitation services are optional for the families and are not an integral part of the intervention. At enrolment and during quarterly follow-up visits, all participating families receive counselling sessions conducted by paediatricians trained in Motivational Interviewing (MI), a client-centred counselling approach aimed at enhancing intrinsic motivation for lifestyle behaviour change. Prior to implementation, paediatricians attend a single 3.5 h training session (online or in person) or provide proof of equivalent prior training. The training is participatory in nature and includes role plays addressing typical counselling situations and challenges in daily practice. All families have access to the fruehstArt web application, where they can communicate with the coach, access a goal-setting tool or recipes, and participate in all study questionnaires. The key components of the intervention are shown in Figure 1.

### 2.2. The Evaluation Design of FruehstArt

The evaluation concept of this study employs a mixed-methods approach, incorporating a summative evaluation, formative evaluations at process and system level, and a health economic analysis. The project is funded by the Joint Federal Committee for a period of 48 months, from 2022 to 2026. The intervention is currently being piloted in North-Rhine-Westphalia, the most populous federal state of Germany.

The summative evaluation is conducted as a randomised controlled trial (RCT) including 812 children. It assesses the effectiveness of fruehstArt by analysing changes in the primary outcome, BMI-SDS, at 12 months in the intervention group (IG) in comparison to the control group (CG). Children are recruited from paediatric practices and obesity centres participating in the project and randomised in a 2:1 (541:271) ratio. Measurements of weight and height are conducted quarterly in paediatric practices.

The IG receives all key components of fruehstArt for 12 months, while families in the CG receive a motivational interview conducted by a paediatrician every four months and the current standard of care. The CG also has limited access to the fruehstArt web application for completing study questionnaires.

Parents will complete questionnaires at three time points: baseline (T0), six months (T1), and 12 months (T2) after enrolment. These questionnaires will be used to collect comprehensive data on a variety of characteristics, including parental health literacy, the child’s daily lifestyle habits, the parents’ level of physical activity and the parents’ quality of life. In addition, a motor skills test (side-to-side jumping), conducted by coaches and study coordinators at baseline (T0) and after 12 months (T2), is included as part of the summative evaluation to assess potential changes in children’s physical competence in relation to physical activity and weight development [29].

A more detailed overview of the overall evaluation design of fruehstArt can be found in the study protocol of the overall study [28]. The methodology relevant to this formative evaluation will be described below.

### 2.3. Objectives and Research Questions

The formative evaluation at the process level aims to identify barriers and facilitators of fruehstArt, the quality of the intervention, and the feasibility of implementation strategies. It also aims to describe and understand the contextual factors of the intervention to provide recommendations for adapting fruehstArt.

Based on the research objectives, the research questions that are addressed are as follows: What factors facilitate or hinder the implementation of the intervention components?What is the quality of implementation of fruehstArt and what differences can be observed between the families?Does implementation quality influence the effectiveness of the fruehstArt intervention?

### 2.4. Study Design

The formative evaluation strategy is based on a mixed-methods approach, incorporating both qualitative and quantitative data. This involves conducting interviews with participating parents, coaches, and paediatricians at two time points to gain a longitudinal understanding of their experiences and perspectives. Quantitative data will be collected to develop an index for measuring implementation quality. Both methods will be used following the recommendations of the UK Medical Research Council [30]. A schematic overview of the design of the formative evaluation at the process level is provided in Figure 2.

### 2.5. Participants and Recruitment Strategies

Participant recruitment for this study began in December 2023 and was completed in March 2024. Data collection is ongoing and is expected to continue until April 2026. The final data export is scheduled for June 2026, after which data analysis will be conducted.

Interviews

**Families** (*n* = 15 to 20) will be considered for an interview based on the assumption that this number is sufficient to reach theoretical saturation in qualitative research [31]. Families allocated to the intervention group will be selected based on the following criteria: BMI-SDS, age, gender, migration background, SES, and coaching strand. To ensure a heterogeneous sample, attention will be paid to distribution balance across these criteria. Families will be recruited every three months to include participants from different stages of study progression. The initial interview will be conducted between two and four months after the start of the intervention. A follow-up interview will be conducted between two and four months before the intervention ends.

**Paediatricians** (*n* = 10 to 15) will be considered for their first interview based on the assumption that this number is sufficient to obtain meaningful insights while ensuring theoretical saturation. They will be invited for an interview if at least four children have been assigned to their practice, ensuring they have acquired sufficient experience with the project’s processes to provide valuable reflections. The second interview is planned to take place two to four months before the end of fruehstArt. Paediatricians will be selected based on the following criteria: region and the number of children from the intervention group assigned to their practice. The number of interviews with paediatricians is lower, as the total number of participating paediatricians is considerably smaller than that of the families. However, this number remains flexible, and additional paediatricians will be recruited if necessary, e.g., if saturation is not reached.

**Coaches** (*n* = 14 in total) will be eligible for their interview once they have coached four families and delivered at least four coaching sessions per family. To identify changes that occur over the course of the project the second interview will be conducted two to four months before the end of fruehstArt.

Potential interviewees will be contacted via email or postal letter and provided with study details. They can choose between in-person, online, or telephone interviews, which will last approximately one hour, be conducted by one researcher, and audio recorded with written consent.

Implementation Quality Index

Quantitative data to measure the Implementation Quality Index will be collected at T1 and T2 from both the coaches (n = 14) and all parents (n = 541) in the intervention group. No separate sample size estimation was conducted for the formative evaluation, as it builds on the intervention group of the summative evaluation, for which a sample size calculation was performed. Data will be used from the fruehstArt app that includes a questionnaire specifically tailored and developed for the purpose of the formative evaluation study.

### 2.6. Instruments

Interviews

Interview guides were developed based on the Consolidated Framework for Implementation Research (CFIR) and consist of open-ended questions and probes to elaborate on answers for clarification [32,33]. The CFIR provides a comprehensive approach to understanding implementation factors across various settings and has been widely used in numerous formative evaluation studies to successfully identify context-specific barriers and facilitators during the implementation process, including mental health programmes [34] or obesity prevention programmes [35,36]. The CFIR comprises five major domains: (1) intervention characteristics, (2) inner setting, (3) outer setting, (4) characteristics of individuals involved, and (5) implementation process. These five domains are further categorised into 39 constructs and sub-constructs presenting implementation factors. A full description of the framework, including relevant interview questions and complete interview guides, can be found in Supplementary Materials Table S1. A brief description of the framework domains, including exemplary questions, is presented in Table 1. Prior to data collection, the interview guides were pilot-tested with the study coordinators, who are familiar with the context and all three target groups. Their feedback informed minor revisions to improve clarity, relevance, and flow of questions. This iterative process ensured face validity of the interview instruments and their suitability for the intended purpose. To reduce potential social desirability bias, participation was voluntary and respondents were assured of confidentiality and anonymity. Interviews were conducted by trained researchers not involved in the intervention delivery, who emphasised the importance of honest and authentic responses.

Implementation Quality Index

As various research studies have demonstrated, implementation quality is a crucial factor in successful implementation of an intervention [37]. To capture this, we will develop an Implementation Quality Index for each participating family based on Dowling and Barry’s framework [38]. This index will assess the following dimensions of the intervention:**Dosage**: The quantity of intervention modules used, such as the number and duration of coaching sessions, rehabilitation services accessed, and the utilisation of the fruehstArt application.**Adherence**: The extent to which the intervention was delivered as intended (fidelity), including adherence to coaching guidelines and any deviations.**Quality of Delivery**: The assessment of how well the intervention was delivered, as reflected in parents’ evaluations of their relationship with coaches and the coaching sessions themselves.**Responsiveness**: Participants’ engagement with the intervention, including parents’ feedback on the fruehstArt web application and coaches’ evaluations of parental involvement.

These dimensions were specifically operationalised for fruehstArt. To establish face validity, the Implementation Index questions were pre-tested with parents not enrolled in this study to ensure that all items were clearly understood. Feedback from this pilot testing informed minor revisions to improve wording and clarity. Table 1 provides a detailed breakdown of the indicators.

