For the quantitative data analysis, all indicator values are aggregated at the family level and converted into a percentage value following the procedure outlined by Dowling and Barry [38]. This allows the individual indicator values within a dimension to be merged into an overall value between 0 and 1 for the respective dimension. The four overall ratings of the dimensions (dosage, adherence, quality of delivery, and responsiveness) are subsequently combined to yield a mean value for the overall quality of implementation.$$\begin{array}{c} Total\;Implementation\;Quality\\ =\frac{\left(Total\;Dosage+Total\;Adherence+Total\;Quality\;of\;Delivery+Total\;Participant\;Responsiveness\right)}{4} \end{array}$$

The items and indicators are not weighted, ensuring that all dimensions contribute equally to the quality of implementation. The visual binning method [40] is utilised to divide the overall assessment into four distinct categories, which are defined by the mean value and ±1 standard deviation: low implementation quality, moderately low implementation quality, moderate high implementation quality, and high implementation quality. Consequently, the families are allocated to the corresponding level of implementation quality. 

Missing data will be handled using an Available Case Analysis (ACA) approach, assuming data are Missing Completely at Random (MCAR). In line with Dowling and Barry [38], cases with more than 25% missing data in key variables will be excluded from the analysis to avoid bias and maintain the reliability of results.

Impact of Implementation Quality on fruehstArt effectiveness (Research Question 3)

Mixed models for repeated measures will be used to analyse the relationship between the Implementation Quality and the primary (BMI-SDS) and secondary outcomes (see [28]) of the effectiveness analysis (summative evaluation).

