**Figure 3 children-12-01613-f003:**
[figure not shown]
fruehstArt intervention model.

**Table 1 children-12-01613-t001:** Overview of quantitative and qualitative indicators.

	Main Research Question	Implementation Outcome	Definition	Participants	Example Questions	Time of Evaluation
**Implementation Quality Index** *(data source: fruehstArt app and questionnaire data)*	** *What is the implementation quality of fruehstArt?* **	*Dosage*	*Quantity of the intervention or intervention modules implemented and used*	*N = 541 Parents* *N = 14 Coaches*	*How often do you use the fruehstArt app (Parents)?* Reply options: 1 = less than once a month to 7 = multiple times per day *How long did the home visit last? (Coaches)* *Reply option:* *Duration in minutes*	*T1 and T2* *(6-month and 12-month follow-up)*
		*Adherence*	*The extent to which the intervention or intervention modules were implemented as intended*	*N = 14 Coaches*	The coaching sessions have been implemented as planned. *(Coaches)* Reply options: 1 = Does not apply to 4 = Fully applies	
		*Quality of delivery*	*Refers to how well the service providers implement an intervention or intervention modules*	*N = 541 Parents*	*How would you describe the quality of your collaboration with your coach? (Parents)* Reply options: 5 = Really good to 1 = Really bad	
		*Participant responsiveness*	*Subsumes the participants’ reactions to, and handling of the intervention*	*N = 541 Parents* *N = 14 Coaches*	*I have been able to put the content of the previous coaching sessions into practice (Parents)* Reply options: 1 = Strongly disagree To 4 = Strongly agree *How well did the family respond to the counselling methods used? (Coaches)* Reply options: 1 = Really responsive to 5 = not at all responsive	

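### Dosage is defined as quantity used with no stated denominator, and includes optional rehabilitation offered only above P97, so the Implementation Quality Index can partly reflect strand and severity

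*Protocol article*

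**What the plan says.** Section 2.6 of the protocol article builds one index per family from four dimensions. It describes Dosage as "The quantity of intervention modules used, such as the number and duration of coaching sessions, rehabilitation services accessed", together with use of the app. Table 1 gives "Quantity of the intervention or intervention modules implemented and used". Neither wording refers to the amount planned for the family, whereas Adherence is defined in both places against what was intended.

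Section 2.1 makes the planned amount depend on the child and family. "Children are assigned to one of six coaching strands depending on the child’s BMI percentile and individual support needs", and, according to family needs, "the number of coaching sessions varies, ranging from 10 to 20 home visits within the 12-month intervention period". On rehabilitation, "those with a BMI above the 97th percentile are offered a six-week inpatient rehabilitation service" or an outpatient alternative, but "the rehabilitation services are optional for the families and are not an integral part of the intervention". Enrolment is wider than that group: it covers children who are "overweight (Body Mass Index (BMI) > P (Percentile) 90) or obese (BMI > P97", and also some with a rapid rise in BMI-SDS.

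Section 2.7 says that "all indicator values are aggregated at the family level and converted into a percentage value", by the procedure of the cited source index. It does not say what the percentage is a percentage of. The four dimensions are averaged with equal weight, and the total is cut into four levels at the mean and one standard deviation either side (research question 2). Mixed models then relate the index to BMI-SDS and the secondary outcomes (research question 3). The index exists only for the 541 families of the intervention group. The limitations in the Discussion cover equal weighting, coach self-assessment and the lack of psychometric testing, but not this point.

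**The concern.** A measure of implementation quality should be high when a family received what was planned for it. If one of its four parts is an amount, and the amount is set by BMI percentile and need, two families who were served equally well can receive different scores.

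Research question 2 asks how families differ, and part of the answer could simply be the strand to which they were assigned. Research question 3 relates the index to BMI-SDS, and BMI is one of the things that decides the strand. That comparison lies within the intervention group, so randomisation does not balance it.

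Rehabilitation is the firmest part of the concern because it does not depend on the missing denominator. The article places it outside the intervention proper, yet counts it towards how well the intervention was implemented.

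**Working it through.** The article gives no numerical example of the index, so there is no figure to reproduce. The inputs from the document are the range of 10 to 20 visits and the P97 threshold (section 2.1), the Dosage components (section 2.6) and the formula Total = (Dosage + Adherence + Quality of Delivery + Responsiveness) / 4 (section 2.7). Everything else below is an assumption.

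**1. Visits alone.** Family A completes a plan of 10 visits and family B a plan of 20. They are equal on the other three dimensions.
- Common denominator of 20 (assumed): A = 10/20 = 0.50, B = 20/20 = 1.00, difference 0.50. If visits were the only Dosage indicator, the total index differs by 0.50/4 = 0.125. If visits are one of four equally weighted Dosage indicators, it differs by 0.50/(4 × 4) = 0.031.
- Own plan as denominator: A = 10/10 = 1.00, B = 20/20 = 1.00, difference 0.

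**2. Rehabilitation added.** Dosage is taken as the mean of four indicators: visits, duration, app use and rehabilitation (1 if used, 0 if not). Duration and app use are set at 0.7 for both families. Family A's child is at or below P97 and not offered rehabilitation; family B's child is above P97. That the child above P97 also has the longer plan is part of the assumption. For example, in the first row A = (0.7 + 0.7 + 0.5 + 0)/4 = 0.475 and B = (0.7 + 0.7 + 1 + 1)/4 = 0.850, so the total differs by 0.375/4 = 0.094.

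| Visit denominator | Rehabilitation if not offered | Dosage A | Dosage B, used | Total, B − A | Dosage B, declined | Total, B − A |
|---|---|---|---|---|---|---|
| 20 | scored 0 | 0.475 | 0.850 | +0.094 | 0.600 | +0.031 |
| 20 | left out | 0.633 | 0.850 | +0.054 | 0.600 | −0.008 |
| own plan | scored 0 | 0.600 | 0.850 | +0.063 | 0.600 | 0 |
| own plan | left out | 0.800 | 0.850 | +0.013 | 0.600 | −0.050 |
| own plan | removed for all | 0.800 | 0.800 | 0 | 0.800 | 0 |

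Both families completed their visit plans in every row. Only the last row gives them equal scores whatever B does about the optional service. The sign of the gap changes with the scoring rule and with B's choice.

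**3. Effect on the BMI-SDS analysis.** A null simulation (n = 541, 1,000 runs per setting) had no true effect of implementation. It assumed:
- baseline BMI-SDS with mean 2.0 and SD 0.6, and need correlated 0.7 with it;
- planned visits of 15 + 3 × standardised need, rounded and held to 10 to 20, with a delivered share of mean 0.85 and SD 0.10;
- visits as the only Dosage indicator, and other dimensions with mean 0.75 and SD 0.05 to 0.15;
- 12-month BMI-SDS equal to baseline plus noise with SD 0.3.

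Rejection at |t| > 1.96:
- Denominator 20, no baseline adjustment: 100% of runs.
- Denominator 20, adjusted for baseline: 3.5% to 5.2%.
- Own-plan denominator, no adjustment: 3.3% to 4.1%.

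Here need acts on the outcome only through baseline BMI-SDS. If need also drives later weight gain, baseline adjustment alone would not remove all the bias.

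**The case against.** Section 2.6 says what Dosage covers, not how it is scored. Section 2.7 does the scoring by percentage, and a percentage needs a reference amount, which could be each family's own plan; in that case the visit problem vanishes. An article may leave such detail, and model covariates, to the full protocol or analysis plan. This stands: scoring by raw count is not established, and the denominator of 20 is an assumption.

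Delivery relative to plan is already captured by Adherence, and amount received is a legitimate separate dimension. This stands in part. An own-plan Dosage would overlap with Adherence, but the Adherence item shown in Table 1 is a four-point coach rating, not a count of visits held against visits planned.

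Dosage is only a quarter of the index and visits only one of its indicators, so any distortion is diluted. This also stands, as the fall from 0.125 to 0.031 in step 1 shows.

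A reader might infer that heavier children score as better implemented, and that a beneficial effect of delivery would therefore appear as harm. The documents do not support this. They never say that a higher BMI brings more visits, a declined rehabilitation offer can lower a heavier child's score, and the unadjusted comparison that would produce such a result is not the analysis stated. A reader might also infer that quarterly paediatric counselling was left out of Dosage. The list in section 2.6 is illustrative and Table 1 shows example questions, so that does not follow.

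None of this answers the rehabilitation item. Its inclusion is stated, and neither way of scoring it for children who are not offered it is satisfactory.

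**Conclusion.** The point holds as a defect in the definition of Dosage, not as demonstrated confounding. The article counts an optional service, restricted to children above P97 and described as non-integral, towards implementation quality. It also defines the rest of Dosage by quantity under plans that vary with need, without fixing the denominator.

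On an assumed common denominator of 20, equally complete delivery can differ by 0.50 in visit dosage and by up to 0.125 in the total index. On an own-plan denominator the visit gap is 0. With own-plan visits, rehabilitation still moves the total by −0.050 to +0.063 in the worked example. Whether such gaps move a family between quality levels depends on the standard deviation of the index, which the article does not give.

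The levels in research question 2 and the relation to BMI-SDS in research question 3 can therefore partly reflect strand and severity. The documents show neither the size nor the direction of that effect. Baseline adjustment would remove much of the bias in research question 3 but would not repair the descriptive levels in research question 2.

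**What to change.** State the denominator in section 2.7: score visits as visits held divided by visits planned for the child's own strand or counselling plan, capped at 1. Take rehabilitation out of the index and report its uptake separately for children above P97. Adjust the model for research question 3 for baseline BMI-SDS and coaching strand. Reconcile the status of rehabilitation in section 2.1 with its listing in section 2.6.

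The cost is rescoring and a few lines in the analysis plan. Section 2.5 schedules the final data export for June 2026 with analysis afterwards, so this can be settled before any results are seen. The downsides are a slight departure from the source index, some overlap with Adherence, and the need for planned visit counts. Section 2.1 describes a customised counselling plan for each child, but the article does not say whether planned visit numbers are stored.
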